### Interventions

Both patient groups will receive the standard presurgical work-up including CT imaging, quality of life questionnaires, functional evaluation of both donor sites, and a functional evaluation of bite force and jaw mobility.

Experimental arm - VSP: The trial research engineer (RE), located at VGH, will segment the CT data to create a 3D model for surgical planning. During the teleconference between site surgeon (SS) and RE, the RE will load the CT data and the segmented 3D model into the virtual planning environment. With the RE navigating the software, which was created in-house at VGH and used in a previous case series, the SS will determine the extent of the disease and define the resection planes [44–51]. After the cutting planes are created, the RE will use the software to create the reconstruction plan with either the patient-specific fibula or scapula, from which the donor bone will be chosen based on the reconstructive cephalometrics. Once the surgeon is satisfied with the plan, the teleconference will end and the RE will create and 3D print the surgical guides for the mandible, for the fibula or scapula, as well as the 3D computed reconstruction (Fig. 1). The surgical cutting guides will be sterilized at VGH’s Medical Device Reprocessing Department and couriered to the SS. The 3D reconstruction model, not requiring sterilization, will be sent directly to the SS. Prior to surgery, the SS will prebend a titanium fixation plate to the reconstruction model and send it for sterilization at the host’s hospital. The planning process, including shipping, will take at most 6 business days. The SS’s medical office assistant is responsible for receiving the shipments and transferring them to the SS. During surgery, the SS will employ the cutting guides and pre-bent titanium plate (Fig. 2). The mandibular cutting guides will be used to guide the resection, and the pre-bent plate is then applied to the remaining native mandible. Next, either the fibular or scapular cutting guide is applied to harvest the donor bone, which is then secured to the plate, followed by re-vascularization of the flap at the head and neck. If the planned resection cannot proceed (possibly due to extensive tumour growth since the time of surgical booking), the surgical team will note the reason for abandonment and conduct a standard FHS.

**Fig. 1 Fig1:**
[figure not shown]
Overview of the VSP workflow. Pre-op: Segmentation of a diseased mandible. Planning: Cutting planes virtually defined on the diseased mandible. Reconstructions are planned using the fibula (top half) or scapula (bottom half). The planned reconstruction, the customized mandible cutting guide and the custom fibula/scapula cutting guides are shown. Post-op: segmentation of the post-operative CT of the reconstructed mandible

**Fig. 2 Fig2:**
[figure not shown]
Intraoperative use of fibular cutting guide (left), mandibular cutting guide (centre) and scapular cutting guide (right)

All SS will attend an initial ex-vivo training workshop hosted at VGH, plan a prospective VSP case, and observe the SS-VGH perform a VSP surgery. Each participating site must demonstrate the successful completion of VSP for 5 cases before randomizing patients in the trial. The SS all have prior experience with the VSP process through their medical training. The training workshop and 5-case requirement allows the SS to identify specific issues associated with VSP workflow at their sites. Based on the number of patients eligible for recruitment to the study, we estimate that the 5-case requirement will take at most 6 months to complete.

Control arm - FHS. In FHS, the SS will proceed with surgery as per the institution’s routine practice. The donor bone will be selected based on clinical and radiological presentation, along with a patient preference-based clinical discussion (Fig. 3).

**Fig. 3 Fig3:**
[figure not shown]
Study schema

### Allocation: sequence generation and implementation

The surgeons at each site will screen all patients for eligibility at the time of their preoperative appointment. Patients who express an interest in participating will meet with the local site research coordinator (LSRC) during the same visit to review the study. If the patient consents at the time of the clinic visit, all baseline data collection will be done at that time. If the patient consents after the visit the LSRC will arrange for a clinic visit to collect the baseline data. After baseline data collection is complete, the baseline CT scan will be uploaded to the REDCap database and reviewed by the research engineer. After confirmation of eligibility, the RE will access REDCap to randomize the patient. Randomization will be centralized, web-based and concealed using the randomization function within REDCap. Patients will be randomized in a 1:1 ratio. Treatment allocation will be stratified by hospital site and disease type: noncancer/cancer. Permuted blocks of varying sizes will be employed and will be unknown to study personnel. An independent statistician will create the randomization list and upload the list to the REDCap database.

This is a single-blind study as the SS will not be blinded to the intervention since they will be applying the guides during the reconstruction surgery procedure. After the randomization list is uploaded onto REDCap, the LSRC who will be performing the data collection, the radiologists who will be performing the bony union analysis, the oral surgeons/prosthodontists who will be performing dental rehabilitation assessments, and the statistician and statistical graduate students who will be performing the statistical analysis will not have access to the list as they will be blinded to the intervention.

### Treatment and follow-up

Patients will have their surgery scheduled according to local practice. Those patients randomized to the VSP arm will need a minimum of 6 business days from consent to surgery to allow for the production and shipping of the surgical guides. A comparable delay in the FHS arm will not be present, however most patients wait on average 3–4 weeks between consent and surgery.

Participants will be followed during their hospital stay (on average 7–10 days) and at standard clinic intervals (1-, 6-, and 12- months post-surgery) (Table 1).

**Table 1 Tab1:** Schedule of events

Schedule of events	Enrollment			Follow-up				Close-out
	Baseline visit	Allocation	Before surgery	5 days	1 m	6 m	12 m	
Screen for eligibility	X							
Informed consent	X							
Allocation		X						
Screen for adverse events					X	X	X	
Head and neck; abdominal or leg CT scans			X (at least 6 days prior to surgery)	X			X	
Virtual surgical planning; guides 3D printed, sterilized, and shipped to participating sites			X					
Clinical Measurements (jaw mobility, bite force)	X				X	X	X	
Surveys (UW-QOL, EQ-5D-5 L, MDADI, LLTQ/DASH, GOHAI) and HUQ	X				X	X	X	
Data analysis								X
Publication								X

The patient population under study (60% squamous cell carcinoma, 10% ameloblastoma, 7.5% osteosarcoma, 15% osteoradionecrosis, and 7.5% other) have a serious illness and are largely compliant with scheduled follow-up. To maintain desired precision (power), we have incorporated a 5% loss to follow up in our sample size calculation. We anticipate 10% will die within the 1st year of surgery based on the AJCC staging manual and historical site data [52]. Deaths will be considered a competing risk to non-union in the analysis.

### Statistics and sample size calculation

The primary estimand of interest is the between-group difference in the proportion of trial patients who have a nonunion at 1 year. Point and interval estimates for the between-group difference at 1 year will be determined using the Fine-Grey competing risk regression model with treatment group as a covariate and a robust standard error to account for within-centre homogeneity of the outcome. Participants will be analyzed according to their treatment allocation regardless of treatment received (treatment policy perspective). In the primary analysis we assume that losses to follow-up (censoring) are unrelated to outcome.

Assuming 20% (FHS) vs. 10% (VSP) nonunion at 1 year, 15% mortality before 1 year, 5% loss to follow up before 1 year, beta = 0.20 and alpha = 0.05 (2-sided) yields a total of 420 randomized patients (210/arm). This sample size was determined based on 10,000 simulations incorporating the proposed analytic strategy. Across 7 participating centres and accounting for estimated loss to follow-up and mortality rates, we anticipate recruiting approximately 140 patients per year thus target recruitment should be met within 3 years.

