### Primary outcome

The primary outcome is non-union as assessed by two independent radiologists at the Vancouver General Hospital (VGH), blinded to the intervention, based on the 12-month postoperative CT scan. Each apposition (between native bone and the donor bone, or between flap segments) will be assessed as non-union, partial union, and complete union. Cases with a disagreement between reviewers will undergo consensus review, and any persisting disagreements will be reviewed by a third radiologist and classification will be based on the majority vote. The non-union rate was chosen as the primary outcome due to the clinical impact of non-union on the potential development of wound complications [10, 19]. As well, based on a retrospective review of non-union data at the VGH, there is a significant difference in non-union rate between patients who underwent FHS and VSP facilitated oromaxillofacial reconstruction.

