### Statistical methods

Primary outcome: the primary estimand of interest is the between-group difference in the proportion of patients with a nonunion at 12 months in the full trial population grouped according to their treatment allocation (treatment policy estimand). Point and interval estimates for the between-group difference will be determined from a competing risk model that incorporates death as a competing risk.

Losses to follow-up will be censored at the last study visit. If the loss to follow up for the primary outcome is > 5% overall or in either treatment group, a sensitivity analysis will be conducted using a weighted generalized estimating equation approach. Secondary repeatedly measured, continuous outcomes will be analyzed using a linear mixed-effects model with a random effect for patient nested within study center. Structural accuracy, which has 4 measures: mandibular width and projection deviation, deviation in donor bone segment lengths and angles, will be compared with O’Brien’s global test to obtain an overall assessment of the intervention on the 4 accuracy measurements. O’Brien’s test is sensitive to effects that are consistent across the multiple measures increasing power, while simultaneously lowering type 1 error rates.

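### The primary risk difference is taken from a Fine-Gray time-to-event model although non-union is read once, at 12 months, so the estimate depends on how time and ties are coded

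*Protocol article*

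**What the plan says.** The section *Primary outcome* of the protocol article defines the endpoint as a radiological status: "The primary outcome is non-union as assessed by two independent radiologists at the Vancouver General Hospital (VGH), blinded to the intervention". The same sentence ties the reading to a single scan; it is made "based on the 12-month postoperative CT scan". Table 1 lists CT before surgery, at 5 days and at 12 months, and none at the 1- and 6-month visits.

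The section *Statistics and sample size calculation* names the target: "The primary estimand of interest is the between-group difference in the proportion of trial patients who have a nonunion at 1 year". It then names the estimator: "Point and interval estimates for the between-group difference at 1 year will be determined using the Fine-Grey competing risk regression model". Treatment is the covariate, and the standard error is made robust to clustering by centre. The section *Statistical methods* is less specific: "Point and interval estimates for the between-group difference will be determined from a competing risk model that incorporates death as a competing risk".

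Two rules bear on time. On deaths: "Deaths will be considered a competing risk to non-union in the analysis". On losses: "Losses to follow-up will be censored at the last study visit". The article does not say what time a non-union receives, or when a patient whose 12-month CT shows no non-union leaves the risk set.

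**The concern.** Fine-Gray regression models the subdistribution hazard of an event that happens at a time. Its parameter is a hazard ratio. A difference in 1-year proportions has to be rebuilt from that ratio and a cumulative baseline hazard, and the baseline hazard comes from the event times. Here the only times available are the nominal visit or the date of the scan, and neither is the onset of non-union.

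The fitted 1-year risks can therefore reflect coding choices as well as the share of patients with non-union. Two analysts following the same text could report different differences and intervals from the same patients. That matters because the article makes the difference with its interval the primary result, and because the sample size rests on simulations of this strategy.

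**Working it through.** **Inputs from the section *Statistics and sample size calculation*.** "Assuming 20% (FHS) vs. 10% (VSP) nonunion at 1 year, 15% mortality before 1 year, 5% loss to follow up before 1 year"; two-sided alpha 0.05, power 80%, 210 per arm.

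**1. The plan's own figure.** Two-proportion formula, pooled variance under the null:

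n = [1.96 × √(2 × 0.15 × 0.85) + 0.8416 × √(0.20 × 0.80 + 0.10 × 0.90)]² / 0.10² = 198.97, so 199 per arm.

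Allowing for 5% loss: 199 / 0.95 = 209.5, so 210 per arm and 420 in total. The stated figure is reproduced when 20% and 10% are read as shares of all randomised patients, with deaths kept in the denominator. The true difference is then 10 points.

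**2. Every read coded at month 12.** Take 40/200 and 20/200 events, all tied at one time.
- Breslow ties: hazard ratio = (20/200)/(40/200) = 0.50. Baseline increment = 60/(200 + 200 × 0.50) = 0.20. Fitted risks are 1 − exp(−0.20) = 18.1% and 1 − exp(−0.10) = 9.5%; difference 8.6 points.
- Efron ties: hazard ratio 0.473, baseline increment 0.2226. Fitted risks are 20.0% and 10.0%; difference 9.96 points.

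**3. Reads coded at the actual scan date, patients without non-union censored at their scan.** The article gives neither this coding nor a CT window, so the share f scanned by the 1-year evaluation time is an assumption. When a share u has been scanned, the risk set has shrunk to 1 − u. The cumulative subdistribution hazard is p × ∫ du/(1 − u) from 0 to f, which is −p × ln(1 − f). The fitted risk is 1 − (1 − f)^p.

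| Share scanned by 1 year (assumed) | FHS, p = 0.20 | VSP, p = 0.10 | Difference |
|---|---|---|---|
| 0.25 | 5.6% | 2.8% | 2.8 points |
| 0.50 | 12.9% | 6.7% | 6.2 points |
| 0.75 | 24.2% | 12.9% | 11.3 points |

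**4. Simulation at 210 per arm with 15% deaths and 5% loss.** Further assumptions: deaths uniform over the year, losses at the 1- or 6-month visit.
- Month-12 coding with Breslow ties: mean difference 8.6 points; a 95% interval covers about 93%.
- Scan-date coding, scans spread evenly within 1 month either side of month 12: about 6.2 points; coverage about 67%. Halving the spread does not help (about 6.1 points), because half the scans still fall after month 12.
- Non-union at its scan date, but patients without it censored at a common later date: 5.3 points read at exactly month 12, and 10.1 at the end of the scan window.
- Direct risk difference at the 12-month CT: 9.8 to 10.0 points in every scenario.

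**5. The test.** Across codings the subdistribution hazard ratio stays at 0.47 to 0.50, and rejection under the null at 0.03 to 0.05. Rejection under the alternative is 0.73 to 0.83 with the model-based standard error. The planned centre-robust standard error was not simulated.

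**The case against.** The strongest reply is that the large distortions need a coding the article does not state. Its times are nominal (1 year, 12 months, a 12-month column in Table 1), and its only censoring rule concerns losses to follow-up. Nothing says that a patient with a completed CT and no non-union is censored on the scan date. On the nominal reading, with one binary covariate and one event time, the model is saturated and tie handling alone decides the result: the error is nil with Efron ties and 1.4 points with Breslow ties. Tie method and nominal versus actual dates are matters for a statistical analysis plan, which is not shown. All of this stands, and it limits the size of the point.

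It does not remove the point. A missing tie rule would be no finding in itself. What the article does fix is a time-to-event estimator for a status observed at one time, and it makes that estimator the source of the primary point and interval estimates. Under the favourable coding the model adds only that deaths stay in the denominator and that losses are weighted, and both can be had without any dependence on ties.

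A reader might infer that Fine-Gray regression cannot deliver this estimand, that the headline result will be biased, or that the primary test is invalid. The documents support none of these. Nominal coding with Efron ties recovers the estimand. Scan-date coding and the spread of scan dates are assumptions made here. Type I error holds. The coding used in the protocol's 10,000 simulations is not described, so it cannot be assumed to be a harmful one.

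**Conclusion.** The mismatch is real and lies in the stated method: an outcome without an event time is assigned a model that needs one. Its consequence is conditional. Against a true 10 points, the reported difference is about 10.0 or 8.6 with nominal month-12 coding (Efron or Breslow ties). It could be about 3 to 11 with scan-date coding and censoring at the scan, if between 25% and 75% of scans are done by 1 year. The harm is to the effect estimate and its interval. The hazard ratio and type I error are largely unaffected. Power under some codings fell to about 0.73, but only the model-based standard error was examined, so no firm claim on power follows.

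**What to change.** In the sections *Statistics and sample size calculation* and *Statistical methods*, estimate the 12-month risk in each arm directly:

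- Status is 1 if non-union is read on the 12-month CT, whatever its actual date. Status is 0 if none is read or the patient died before that CT. Deaths thus stay in the denominator, as a competing-risk target requires.
- Report the risk difference with its interval, from binomial or standardised logistic regression. If a competing-risk form is preferred, use Aalen-Johansen or pseudo-values with every read assigned to nominal month 12. The wording in *Statistical methods* already leaves room for this.
- Handle losses under the stated assumption that they are unrelated to outcome, or by weights, and say which.
- Keep the planned centre-robust standard error.
- Keep the subdistribution hazard ratio as a supportive measure only.

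Re-run the sample-size simulation with this estimator. No more patients are expected. With 210 × 0.95 = 199.5 evaluable per arm, power is Φ{[0.10 − 1.96 × √(2 × 0.15 × 0.85/199.5)] / √(0.25/199.5)} = Φ(0.845) = 80.1%. Simulation of the direct risk difference at 210 per arm, without centre effects, gave power 0.81 and type I error 0.049. So 420 stands, and the cost is a wording change and the re-run.

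### The primary Fine-Gray model leaves out disease type and has no site term, although randomisation is stratified on both; the analysis does not match the design and gives up a little precision

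*Protocol article*

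**What the plan says.** The section on allocation (sequence generation and implementation) states: "Treatment allocation will be stratified by hospital site and disease type: noncancer/cancer". It also says "Patients will be randomized in a 1:1 ratio".

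The section on statistics and sample size defines the estimand as a between-arm difference in the 1-year proportion with non-union. It estimates this with a "Fine-Grey competing risk regression model with treatment group as a covariate", together with "a robust standard error to account for within-centre homogeneity of the outcome". The later Statistical methods section adds that death is a competing event and that losses are censored. Neither section brings disease type into the primary analysis, and neither makes site a covariate or stratum of the model.

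The sizing inputs are "Assuming 20% (FHS) vs. 10% (VSP) nonunion at 1 year", "15% mortality before 1 year, 5% loss to follow up before 1 year", 80% power and a two-sided 5% level, giving 420 patients over 7 centres. The article adds: "This sample size was determined based on 10,000 simulations incorporating the proposed analytic strategy".

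**The concern.** Stratified randomisation balances the arms on the stratification factors. The usual principle is to carry those factors into the primary analysis, so that the precision bought by the balance is realised. Here one factor is absent from the stated analysis and the other appears only in the variance.

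Disease type may well be prognostic, since the population mixes squamous cell carcinoma and osteosarcoma with ameloblastoma and osteoradionecrosis. The investigators thought it important enough to stratify on. The trial is sized for 80% power with almost nothing to spare, so even a small gain in efficiency is worth having when both factors are already recorded at randomisation.

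**Working it through.** **1. The plan's own sample size.** Inputs: 20% versus 10%, two-sided α 0.05, power 0.80, 5% loss. Deaths stay in the denominator as competing events, so 20% and 10% are read as cumulative incidences. With pooled variance and no continuity correction:

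n = [1.960·√(2·0.15·0.85) + 0.8416·√(0.20·0.80 + 0.10·0.90)]² / 0.10² = (0.9897 + 0.4208)² / 0.01 ≈ 199 per arm.

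199 / 0.95 = 209.5, so 210 per arm and 420 in total. This matches the plan. Power at 210 × 0.95 = 199.5 evaluable per arm is 80.1%.

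**2. Simulation of the stated model.** There were 420 patients in 7 centres of 60, permuted allocation within site × disease, 15% deaths, 5% loss, and 1,500 runs per scenario. Assumptions that the documents do not supply:
- 67.5% cancer (60% squamous cell carcinoma + 7.5% osteosarcoma, with the 7.5% other counted as noncancer);
- disease odds ratio for non-union of 1 to 5;
- site standard deviation (SD) of 0 to 0.8 on the logit scale;
- no treatment-by-site variation.

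**3. Power, model-based standard error (SE):**

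| Disease OR, site SD | Treatment only | Stratified by site × disease | Gain (points) |
|---|---|---|---|
| 1, 0 | 81.7% | 81.7% | 0.0 |
| 2, 0.4 | 81.1% | 81.5% | 0.4 |
| 3, 0.4 | 81.2% | 82.1% | 0.9 |
| 5, 0.8 | 80.5% | 82.8% | 2.3 |

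Each power figure has a Monte Carlo SE of about √(0.81·0.19/1500) = 1.0 point, although the two columns share the same simulated trials. In the last row the null rejection rate also rises, from 2.8% to 3.7%, so part of that gain reflects a less conservative test. On the log subdistribution-hazard scale the gain is not a smaller SE. In the last row the coefficient moves from −0.767 to −0.802 while its empirical SE moves from 0.287 to 0.296, a ratio of 2.67 against 2.71.

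**4. Risk-difference scale.** A simpler comparison used 6,000 runs and unequal sites: an unadjusted against a Mantel-Haenszel risk difference, with no Fine-Gray model and no centre-robust SE.
- OR 3, SD 0.5: mean SE 0.0374 against 0.0364 (ratio 1.027), power 81.4% against 82.7%.
- OR 3, SD 0.7: mean SE 0.0380 against 0.0365 (ratio 1.041), power 79.7% against 81.8%.
- No prognostic strata: no difference.

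Null rejection in the second case was 4.4% against 5.7%, so here too some of the power gain is test size.

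**5. Is the standard error of the treatment-only model too wide?** Under the null:

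| Disease OR, site SD | Empirical SE | Patient-level robust SE (rejection) | Centre-robust SE | Centre-robust rejection, normal | Centre-robust rejection, t on 6 df |
|---|---|---|---|---|---|
| 1, 0 | 0.226 | 0.222 (5.4%) | 0.197 | 12.3% | 6.4% |
| 2, 0.4 | 0.222 | 0.224 (5.3%) | 0.194 | 11.9% | 6.2% |
| 3, 0.4 | 0.226 | 0.224 (5.2%) | 0.194 | 12.2% | 6.3% |
| 5, 0.8 | 0.212 | 0.226 (2.9%) | 0.186 | 12.1% | 6.3% |

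The patient-level SE is clearly too wide only in the last row. The centre-robust SE, which is the one planned, is too narrow throughout: 0.197/0.226 = 0.87, 0.194/0.222 = 0.87, 0.194/0.226 = 0.86 and 0.186/0.212 = 0.88. Adding disease type, or stratifying, leaves its rejection rate at 11.5–12.7% with a normal reference.

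**The case against.** The other side has four good arguments. Site is not ignored, because the same sentence of the plan provides a centre-robust SE. The documents give neither a site variance nor an effect of disease type on non-union, so any gain rests on assumption. The trial was sized by simulating its own analysis, so omitting adjustment forgoes a bonus and does not erode the stated power. And an SAP that is not shown may add covariates.

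The first three stand, and they limit the size of the point. The fourth does not remove it: the article names the model's covariate and says the sizing simulations used the proposed analysis, so the point concerns a stated model and not a detail left open.

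A reader might go further and infer that ignoring the strata makes the planned standard errors too wide and the test conservative. That result belongs to a model-based or patient-level variance with strongly prognostic strata. The plan uses a variance clustered on centre, which already reflects balance achieved within centres. With only 7 clusters it errs in the opposite direction.

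Replacing the analysis by a Mantel-Haenszel or logistic risk difference is also tempting, but as it stands it would discard the plan's handling of deaths and of censored losses.

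**Conclusion.** The mismatch is certain from the text: disease type is a stratification factor and is absent from the stated primary model, and site has no term in it. The consequence is modest, 0 to about 2 power points over the assumed range, and nil if the strata are not prognostic. A reader might infer that the trial is underpowered as a result. The documents do not support this, since 420 is reproduced and the treatment-only model kept 80.5% power or more with a model-based SE in every scenario. Nor do they support a finding of over-wide errors. This is an inexpensive improvement to a stated model, not a threat to the trial's validity.

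The narrowness of a seven-cluster robust SE is the more consequential feature of the same sentence. Adjusting for the strata does not cure it by itself, so the variance should be settled in the same edit. The size of that effect rests on equal centres, a common treatment effect across centres and a normal reference distribution, which the article does not specify.

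**What to change.** Keep the competing-risk analysis, with death as the competing event and losses censored, and change three things.

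1. **Model.** Adjust for, or stratify by, disease type and hospital site, with a pre-specified rule for pooling very small sites. Full crossing gives 7 × 2 = 14 strata. On the assumed mix the noncancer strata average 420 × 0.325 / 7 = 19.5 patients, or about 3 non-unions each at a 15% average rate, so main-effect covariates may behave better than 14 separate baselines.
2. **Estimate.** Adjustment makes the subdistribution hazard ratio conditional. Predict each patient's 1-year cumulative incidence under both arms, average over the trial's strata, and report the difference, which is the stated estimand.
3. **Variance.** With site in the model, use a patient-level robust variance. In the stratified simulation this rejected 4.1–5.8% under the null and gave 82.5–83.6% power. If the centre-clustered SE is kept, use a small-cluster correction or a t reference on 6 df. The t reference brought null rejection in the stratified model to 5.8–6.9%, but power fell to 71–75%.

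The cost is a change of wording, slightly more analysis work and the standardisation step. Both factors are already recorded at randomisation, and N does not change with the first option for the variance. Keeping the centre-clustered SE with the t reference would mean revisiting the power statement.

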### Data and safety monitoring

The Data and Safety Monitoring Committee (DSMC) will consist of a head and neck surgeon with experience in clinical trials, a biostatistician and an expert in virtual surgery. The DSMC is independent from the investigators and team members involved in the trial. The DSMC will meet bimonthly to review any adverse outcomes and complication rates, and will recommend any modifications to the TSC. The DMSC must be sufficiently satisfied with study progress and safety to approve the continuation of the study.

An interim analysis will be performed by an independent statistician after 50% of the sample size have enrolled and completed their 1-year follow up and CT scan. The statistician will report to the DSMC, which will then decide whether to continue the study based on the Peto stopping guideline (two-sided *p* < 0.001). Data collected from the semi-structured interview will be reviewed during this analysis to determine whether sex, gender or other factors affect patient participation in the trial. The TSC will use this data to change recruitment strategy as appropriate.

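### Clustering the primary standard error on only 7 centres, with no few-cluster correction stated, gives the nominal 5% test a true type I error of about 10% to 14%

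*Protocol article*

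**What the plan says.** The protocol's section Statistics and sample size calculation fixes the primary analysis as Fine-Gray competing-risk regression "with treatment group as a covariate and a robust standard error to account for within-centre homogeneity of the outcome". The same section gives the number of centres ("Across 7 participating centres"), the design rates ("Assuming 20% (FHS) vs. 10% (VSP) nonunion at 1 year", with "15% mortality before 1 year, 5% loss to follow up before 1 year") and the size of the trial ("beta = 0.20 and alpha = 0.05 (2-sided) yields a total of 420 randomized patients (210/arm"). It says that the sample size came from 10,000 simulations of the planned analysis, and it reports no simulated type I error.

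On randomisation, the allocation section says: "Treatment allocation will be stratified by hospital site and disease type: noncancer/cancer". Individual patients are allocated 1:1, so both arms occur in every centre.

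On the interim look at half the sample, Data and safety monitoring says: "The statistician will report to the DSMC, which will then decide whether to continue the study based on the Peto stopping guideline", with a two-sided threshold of 0.001. It names neither the test nor the standard error.

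None of these sections, nor Statistical methods, mentions a finite-sample correction, a t reference or any other device for few clusters.

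**The concern.** A robust standard error can account for similarity of outcomes within a centre only if it is clustered on centre; a patient-level sandwich does not do this. A clustered sandwich is estimated from one summed score per centre. With 7 centres it has about 6 degrees of freedom, and without correction it is biased downward by a factor of about 6/7 on the variance scale. Compared with a normal critical value, it rejects too often and gives intervals that are too short. This happens even when outcomes do not differ between centres at all, because the cause is the number of clusters.

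At stake is error control for the primary endpoint of a superiority trial that is meant to inform health authorities and insurers. The Peto threshold is chosen because it should spend almost no alpha at the interim. It would lose that property if it were applied to the same standard error.

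**Working it through.** **Inputs from the protocol:** 7 centres; two-sided alpha 0.05; 20% against 10% non-union; 15% deaths; 5% loss; 420 patients; interim at about 210 patients with threshold 0.001; individual randomisation stratified by site.

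**Assumed, because the protocol gives no values:** intracluster correlation (ICC) of 0 to 0.05; centre sizes equal or unequal; uniform event times.

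**1. The plan's own figure.** Two-proportion formula with pooled variance under the null:

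n = [1.96·√(2·0.15·0.85) + 0.8416·√(0.2·0.8 + 0.1·0.9)]² / 0.10² = (0.9898 + 0.4208)² / 0.01 ≈ 199 per arm.

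Allowing for 5% loss: 199/0.95 = 209.5, so 210 per arm and 420 in total. The stated size is reproduced. Deaths are a competing event and need no inflation here.

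**2. Analytic size with G = 7 equal centres and a normal critical value z.**

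- Uncorrected sandwich: size = P(|t₆| > z·√(6/7)). At 5%, z = 1.96 gives 11.95%. At 0.001, z = 3.29 gives 2.26%.
- With the G/(G-1) factor: size = P(|t₆| > z), giving 9.8% and 1.7%.

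The matching coverage of a nominal 95% interval is 100 − 11.95 = 88.05% and 100 − 9.8 = 90.2%.

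**3. Simulation.** Censoring-weighted Fine-Gray model with treatment as the only covariate, permuted blocks within site and disease type, 15% deaths and 5% loss. There were 4,000 runs per final scenario and 8,000 per interim scenario. The Monte Carlo standard error is about √(0.115·0.885/4,000) = 0.5 points for the final test and √(0.02·0.98/8,000) = 0.16 points for the interim. All entries are rejection rates in %.

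| Scenario | Clustered, uncorrected, normal | Clustered, G/(G-1), normal | Clustered, G/(G-1), t₆ | Patient-level robust |
|---|---|---|---|---|
| Final 5%, equal centres, ICC 0, 20% both arms | 11.2 | 9.2 | 4.6 | 4.5 |
| Final 5%, equal, ICC 0.05, 20% both arms | 11.5 | 9.2 | 4.8 | 4.1 |
| Final 5%, centres of 120 to 20, ICC 0.02, 15% both arms | 13.8 | 11.5 | 6.5 | 4.7 |
| Final 5%, centres of 150 to 15, ICC 0.02, 15% both arms | 14.5 | 11.9 | 6.9 | 4.6 |
| Interim 0.001, equal, ICC 0 | 1.85 | 1.39 | 0.08 | 0.03 |
| Interim 0.001, equal, ICC 0.05 | 2.11 | 1.60 | 0.04 | 0.03 |
| Interim 0.001, centres of 60 to 10, ICC 0.02 | 2.27 | 1.71 | 0.15 | 0.01 |
| Power, equal, ICC 0 | 82.5 | 78.7 | 63.8 | 80.4 |
| Power, equal, ICC 0.05 | 83.6 | 79.9 | 64.7 | 82.3 |
| Power, centres of 120 to 20, ICC 0.02 | 83.2 | 80.2 | 66.4 | 80.4 |

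The model-based variance behaves like the patient-level robust one (4.0% to 4.6% size at the final test). Simpler simulations of the same design widen the power range for the t₆ version to about 63% to 68%.

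**4. Reading.** In the same simulated data the patient-level variance holds its level and the clustered one does not. The inflation therefore comes from clustering on 7 centres, not from the model or the event rate. The patient-level column used a model without site strata; the stratified version was not simulated.

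**The case against.** **The article is condensed.** The correction and the reference distribution are details that a full analysis plan could supply, and the size depends on them. This stands as a condition on the figures: a flat 12% cannot be read from the protocol. It does not remove the point, because the variance estimator itself is stated, and the usual way of carrying it out gives wrong error bars.

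**The interim.** A reader might infer that the 0.001 rule has a true level of about 2%. The protocol names no test for the interim, so this holds only if the primary model is used there.

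**The power simulation.** A reader might also infer that the 10,000 runs inherited the inflated rejection rate. The documents do not show this. The stated 420 follows from a plain two-proportion formula, and an uncorrected clustered test would reach 80% power at about 380 patients. Which variance was coded is unknown.

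**Clustering may have a purpose.** Stratified individual randomisation removes centre main effects from the contrast, but not variation in the treatment effect between centres. Such variation is plausible for a surgeon-delivered technique where a site needs only five completed cases before it randomises. With zero average effect and an assumed between-centre standard deviation of the treatment effect of 0.3 or 0.5 on the logit scale, the patient-level test rejects 6.8% or 10.4% of the time. This also stands. Calling clustering unnecessary is right for the null of no effect with centres taken as fixed, and not beyond that.

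**Conclusion.** The concern holds in conditional form. With a normal reference, the centre-clustered standard error gives the nominal 5% primary test a true size of about 10% (equal centres, G/(G-1) factor) to 12% to 14% (uncorrected, depending on centre sizes), and coverage falls accordingly. These figures assume that the robust standard error is clustered on centre, which is the plain reading, and that no few-cluster method is added elsewhere. The interim level of about 1.5% to 2.5% rests on the further assumption that the same model is used there.

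A t reference on 6 degrees of freedom would roughly restore the size, but not the stated 80% power. So the clustered approach at 420 patients either inflates the type I error or leaves the trial underpowered.

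**What to change.** In the primary analysis, replace the centre-clustered standard error with a patient-level robust (or model-based) variance, and include hospital site as a stratification factor. Use the same variance for the interim test if that test uses this model, and name the interim test. Re-run the power simulation with this stratified analysis and report its simulated type I error alongside power.

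The cost is wording in the protocol and analysis plan and one simulation run, with no extra patients or data. It should be settled before unblinding.

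The statisticians should accept the downside openly: inference then refers to the participating centres and does not allow for random variation in the treatment effect between them. If they want inference beyond these centres and keep the clustered variance, they should state the t reference on 6 degrees of freedom, acknowledge a size of up to about 7% with unequal centres, and revisit the sample size, because power at 420 would be only about 63% to 68%.
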